## Post Approval Submissions

### Modification Information

*To modify an approved study, edit the individual answers that make up the application. The questions below are intended solely for the IRB to have a summary statement of your requested action. The modifications cannot be processed until the actual changes have been made throughout the application.*

1. Provide a brief non-technical summary of any changes you will be making to the study (i.e., study application, project personnel, and/or study documents.) The text you enter here will be reproduced in the IRB approval document, and should contain the details that you and/or your sponsor find relevant (e.g., master protocol/amendment version number and date). Typical summaries are 50-100 words. PLEASE NOTE: THIS SECTION MAY BE EDITED BY THE IRB FOR CLARITY OR LENGTH.

The following changes are requested in this submission:

1. A participating family has asked that both parents be allowed to take part in the study. Allowing both parents to participate will likely improve the outcomes of the intervention, thus we would like to allow both parents to participate if both ask to participate. We will ask the 2nd parent to sign a 2nd consent form and ask them to complete the parent report surveys as well.

2. We are adding a virtual adaptation of the DAYC-2 (protocol has been uploaded) to offer participants more flexibility during telehealth appointments. We will be conducting the assessment with participants in addition to select components of PANDABox, and will only be administered if participants are not engaging in an in-person assessment, or completing the DP-4. Incorporating this measure will not add to the current battery but complement or supplement it accordingly. The addition of this measure will not alter the assessment times described in the current consent form. Because the time estimation is still accurate and the individual measures are not listed in the consent form, we do not plan to re-consent participants currently enrolled.

2. Is this study in Data Analysis only (i.e. enrollment, intervention and follow-up are complete)?

No

Total number of subjects enrolled to date:

30

Is this study currently open to the enrollment of new subjects?

Yes

Total number of subjects actively participating (i.e., Total number of subjects involved in the interventional part of this study. If the study is limited to data collection (e.g., surveys, questionnaires, collection of data from existing records), enter '0':

6

3. Do you have plans to re-consent subjects as a result of this modification?

No

4. Is this modification being submitted in response to Promptly Reportable Information?

No

5. Have the risks as described in A.6., consent form, or any other study document changed?

This may include new risks not previously listed, changes in frequency of known risks, or removal of previously listed risks.

No

### Continuing with Modifications

*Click the "save and continue" button to access your existing application.  
You may make any changes to the application that you are requesting at this time.*

## General Information

### 1. General Information

1. Project Title

Pilot Study: A Parent-Infant Interaction Intervention (PIXI)

2. **Brief Summary.** Provide a **brief non-technical description** of the study, which will be used in IRB documentation as a description of the study. Typical summaries are 50-100 words. Please reply to each item below, retaining the subheading labels already in place, so that reviewers can readily identify the content. PLEASE NOTE: THIS SECTION MAY BE EDITED BY THE IRB FOR CLARITY OR LENGTH.

**Purpose:** The objective is to develop and test, through an iterative process, an intervention to address and support the development of infants with a confirmed diagnosis of neurogenetic disorders that leave individuals at risk for developmental delays or intellectual and developmental disabilities (e.g., fragile X syndrome, Duchesne muscular dystrophy).. The proposed project will capitalize and expand upon existing empirically based interventions designed to improve outcomes for infants with suspected developmental and social delays.

**Participants:** Participants will be infants with a confirmed diagnosis of a neurogenetic disorder within the first year of life and one or both parents. The majority of participants will be identified through Early Check (IRB #18-0009), a voluntary research program in which newborns will be screened for a carefully selected panel of conditions. Additionally, families can self-refer and if they meet eligibility requirements, may enroll in the intervention.

**Procedures (methods):** The intervention, called Parent-infant Interaction Intervention (PIXI) will consist of two phases. Phase 1 will include parent education about early infant development and the neurogenetic disorder for which they were diagnosed. Phase 2 includes direct parent coaching around parent-child interaction based on an empirically based parent-mediated early intervention and repeated comprehensive assessments of family and child functioning.

### 3. Funding Sources

1. Is this project funded (or proposed to be funded) by a contract or grant from an organization EXTERNAL to UNC-Chapel Hill?

Yes

Is UNC-CH the **direct** recipient of any Federal funding for this study? You should answer 'yes' *only* if you are the grantee. You should answer 'no' if you are the recipient of a sub-award or contractor under the grant.

No

Funding Source(s) and/or Sponsor(s): Please list all entities that are providing monetary support or supplies (e.g., study drug, gifts, devices at no cost, or others that provide in-kind services).

| Sponsor Name    | UNC Ramses Number       | Sponsor Type | Prime Sponsor Name | Prime Sponsor Type | Sponsor/Grant Number | Detail               |
|-----------------|-------------------------|--------------|--------------------|--------------------|----------------------|----------------------|
| John Merck Fund | Currently Not Available | Foundation   |                    |                    |                      | view |

2. Is this study funded by UNC-CH (e.g., department funds, internal pilot grants, trust accounts)?

No

3. Is this research classified (e.g. requires governmental security clearance)?

No

4. Is there a master protocol, grant application, or other proposal supporting this submission (check all that apply)?

- ☒ Grant Application
- ☒ Industry/Federal Sponsor Master Protocol
- ☒ Student Dissertation or Thesis Proposal
- ☒ Investigator Initiated Master Protocol
- ☒ Other Study Protocol

## 5. Is this a Clinical Study?

Check YES if this study involves research using human volunteers that is intended to add to medical knowledge. There are two main types of clinical studies: clinical trials and observational studies. Do NOT check yes merely because you are conducting research in a clinical setting or using clinical data.

[Click here for additional definition of "Clinical Study"](#) [figure not shown]

Yes

Does your study ONLY include observational activities?

Observational study: A type of clinical study in which participants are identified as belonging to study groups and are assessed for biomedical or health outcomes. Participants may receive diagnostic, therapeutic, or other types of interventions, but the investigator does not assign participants to a specific interventions/treatment. A patient registry is a type of observational study.

Yes

Will this clinical trial be listed in [ClinicalTrials.gov](https://clinicaltrials.gov), either by you or the sponsor?

[Click here for ClinicalTrials.gov Guidance Information](#) [figure not shown]

Yes

Choose the appropriate Phase designation for this clinical trial.

☒ Pilot Study

☐ Phase I

☐ Phase I/II

☐ Phase II

☐ Phase III

☐ Phase IV

☐ Other

## 4. Screening Questions

*The following questions will help you determine if your project will require IRB review and approval.*

[The first question is whether this is RESEARCH \(click for details\)](#)

1. Does your project involve a systematic investigation, including research development, testing and evaluation, which is designed to develop or contribute to generalizable knowledge? PLEASE NOTE: You should only answer yes if your activity meets all the above.

Yes

[The next questions will determine if there are HUMAN SUBJECTS \(click for details\)](#)

2. Will you be obtaining information or biospecimens through intervention or interaction with the individual, and use, study, or analysis of the information or biospecimens? This would include any communication or interpersonal contact between investigator and subject such as using in-person or online questionnaires/surveys, interviews, focus groups, observations, treatment interventions, etc. PLEASE NOTE: Merely obtaining information FROM an individual does not mean you should answer 'Yes,' unless the information is also ABOUT them.

Yes

3. Will you be obtaining, using, studying, analyzing, or generating identifiable private information or identifiable biospecimens collected through means other than direct interaction? This would include data, records or biological specimens that are currently existing or will be collected in the future for purposes other than this proposed research (e.g., medical records, ongoing collection of specimens for a tissue repository).

OR

Will you be using human specimens that are not individually identifiable for [FDA-regulated in vitro diagnostic \(IVD\) device investigations](#)?

Yes

*The following questions will help build the remainder of your application.*

4. Will subjects be studied in the Clinical and Translational Research Center (CTRC, previously known as the GCRC) or is the CTCRC involved in any other way with the study? (If yes, this application will be reviewed by the CTCRC and additional data will be collected.)

No

5. Does this study directly recruit participants through the UNC Health Care clinical settings for cancer patients **or** does this study have a focus on cancer or a focus on a risk factor for cancer (e.g. increased physical activity to reduce colon cancer incidence) **or** does this study receive funding from a cancer agency, foundation, or other cancer related group? (If yes, this application may require additional review by the Oncology Protocol Review Committee.)

No

6. Is the UNC Chapel Hill IRB taking or being asked to take responsibility for the oversight of research by individuals, groups or organizations outside of UNC Chapel Hill? Or you are asking the UNC Chapel Hill IRB to cede review to an External IRB. If so, a reliance agreement will need to be executed prior to conducting any research activities. [See guidance.](#)

Yes

## 5. Multi-site Study Information

1. Is UNC-CH the Lead Site or Coordinating Center or Sponsor of a multicenter project?

Yes

## Location

1. Are UNC-affiliated researchers involved in research conducted at any locations outside of the United States?

No

## Part A. Questions Common to All Studies

### A.1. Background and Rationale

A.1.1. Provide a summary of the background and rationale for this study (i.e., why is the study needed?). If a complete background and literature review are in an accompanying grant application or other type of proposal, only provide a brief summary here. If there is no proposal, provide a more extensive background and literature review, including references.

Fragile X syndrome (FXS) is the leading known single-gene cause of autism spectrum disorder (ASD) and the most common inherited form of intellectual disability, resulting in significant functional impairments ([name], [name], & Riley, 2017). The mutation of the FMR1 gene has broad implications for the family. Expansions of the gene occur over generations; therefore, identification of one individual with FXS results in the identification of at least one, and often many, additional family members with an FMR1 mutation. Frequently, multiple children are born into a family before a diagnosis is made (Bailey, [name], Bishop, & Holiday, 2009), which leads to broad family consequences ([name], Bailey, Bann, & Bishop, 2014). Despite documentation that symptoms emerge in the first year of life (Burris, Barry-Anwar, Sims, Hagerman, Tassone, & Rivera, 2017; Roberts et al., 2009; Swanson et al., 2018), the average age of diagnosis is 3 years of age for males with FXS (Bailey et al., 2009). Females with FXS and individuals with the premutation are often diagnosed even later as they typically have a less severe phenotype. The delay of diagnosis can reduce timely access to interventions that could have significant consequences for the developmental trajectories of these children. Furthermore, the delay in diagnosis has significantly limited the ability of researchers to understand the natural progression of symptomology and thereby better address treatment options.

Recent initiatives to identify FXS earlier include a national discussion about newborn screening for FXS (Bailey, Skinner, Davis, Whitmarsh, & Powell, 2008; Riley & [name], 2017). Although FXS does not currently meet criteria for a traditional newborn screening panel (NBS), FX is an ideal condition to explore voluntary expanded NBS procedures because of the lack of obvious features at birth, severity, and impact on the broader family system. It is necessary to identify the benefits of early identification to determine whether NBS for FX would be of true benefit to the individual, family, society, and public health support systems.

The rationale for including infants with FXS in this intervention study extends to infants identified with other rare neurogenetic disorders currently not included on traditional newborn screening panels (NBS). The delay in diagnosis has significantly limited the ability of researchers to understand the natural progression of symptomology and thereby better address treatment options. Early access to effective interventions could have significant consequences for the developmental trajectories of these children. In addition, identifying the benefits of early intervention will determine whether NBS for these disorders would be of true benefit to the individual, family, society, and public health support systems.

A.1.2. State the research question(s) (i.e., specific study aims and/or hypotheses).

The primary goal of the proposed project is to develop and test, through an iterative process, an intervention to address and support the development of infants with a confirmed diagnosis of neurogenetic disorders that include a risk for developmental delay or intellectual and developmental disabilities identified at birth through the Early Check program (IRB #18-0009) or eligible self-referrals. PIXI aims to utilize the foundational knowledge available around the development of and early intervention for at-risk infants to both understand the needs of and provide intervention services for families of infants diagnosed presymptomatically with these disorders. We aim 1) develop PIXI with a pilot sample of families, 2) test the preliminary effects of PIXI on infant and parent outcomes. Specific infant outcomes include communication, motor, cognitive skills and

autism spectrum disorder symptoms. Parental outcomes include parenting efficacy.

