**This study will include an open trial of PIXI with a pre-post design. Below is a timeline for participants**

**from pre-enrollment through study completion.****Overall sequence for participants:**

1. Parents enroll in Early Check to permit newborn screening. Parents of infants who screen positive will be contacted and asked to permit confirmatory testing. When confirmatory testing confirms diagnosis, families will attend a genetic counseling session virtually or at the UNC Carolina Institute of Developmental Disabilities (CIDD) to receive this diagnosis and accompanying genetic counseling when the infant is approximately 2-3 months of age.
2. At this Genetic counseling visit, families will be informed about associated studies, including the present PIXI study. Parents who express interest in this study can enroll during this genetic counseling visit or take-home information about PIXI and contact the study team to enroll anytime during the infant's first 12 months of life. Families that wish to further contemplate enrollment in PIXI after their genetic counseling appointment will be called a week after their appointment to assess any further interest in the study. Parents of infants with FXPM diagnosed through Early Check will be invited to participate in PiXI when there are available slots. Eligible families will be provided with information about PIXI and if interested, added to the wait-list. Additionally, families with rare neurogenetic disorders who have not been identified through Early Check may self-refer to the study or be referred by a provider. These families who contact the study team and express interest in the study, will be provided the informational handout (attached). If families wish to enroll, they will be added to the waitlist and, when applicable, will schedule an appointment for their Baseline/Time 1 assessments. After enrollment in the study, the procedures for self-referrals and those identified through Early Check will be identical.

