  7. Families will receive Phase 2 of PIXI following their Time 2 assessment. Initially, Phase 2 followed the British Autism Study of Infant Siblings- Video Feedback Intervention to Promote Positive Parenting (iBASIS-VIPP; Juffer, Bakermans-Kranenburg, & Van IJzendoorn, 2008, Green et al., 2015). Upon review of the first four participants, interventionists felt that the iBASIS-VIPP parent coaching methodology was not effective with this specific population, therefore we propose to use a modified version of Infant Start (Rogers et al. 2014), which utilizes a more concrete and directive coaching methodology. We will work with one of the creators of Infant Start, [name] to modify the intervention to meet the needs of families with FX. [name] will support research team in the training, fidelity, and implementation of the intervention through video observation. [name] will receive no identifiable information other than information which may be disclosed within the video. See section A.11 and the attached contract for further details on her role as an educational consultant and confidentiality agreements. The infant enrolled who is still participating will complete iBASIS VIPP and all future infants enrolled will participate in Infant Start; results will be compared at the end of the intervention. Phase 2 will consist of approximately 6 to 20 sessions occurring on a weekly or biweekly basis. Number of sessions will be based on family availability and need. Sessions will be conducted by a trained interventionist and will occur via telehealth. Some sessions may be conducted in person based on family need. Intervention will target symptoms related to developmental delay and ASD symptomology. The first session of phase 2 will be used to develop treatment goals; interventionist will complete an informal play assessment with parent and child and fill out the Early Start Denver Model Checklist which allows interventionist to inventory child's developmental skills. Interventionist will coach parents in utilization of intervention strategies to meet developmental goals using a variety of everyday routines and play opportunities. Interventionist and family will have opportunity to discuss and review strategies. Interventionist will video record sessions. Video recordings will later be coded for parent responsivity and fidelity. The previous i-BASIS-VIPP program consisted of a combination of up to 12 in-home (scheduled as needed) and telehealth sessions over a period of 5 months. The 10 sessions included (1) a preliminary session to establish goals with the parent, (2) six intervention sessions (delivered weekly to bimonthly) with a theme building on strategies learned and practiced from the previous session, and (3) up to five booster sessions to consolidate learning. In the six intervention sessions, the first two focus on infant behavior (with parent behavior alluded to indirectly), the second two address parent behavior, and the final two sessions examine more complex chains of interaction. Interventionist video recorded parent-child interactions. Video recordings will later be coded for parent responsivity.

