give the child an engaging toy for 30s, gently restrain their arms to prevent engagement for 30s, then return the toy and say, "It's okay [name], you can have it. [Parent] was just teasing." During a bubbles task (to probe for positive affect), the parent will blow bubbles while reading 5 standard prompts. Coding of video will provide measures of positive affect (e.g. smiling), negative affect (e.g. escape behaviors), and heart rate modulation.

- **Story Time:** The examiner will cue the parent to read a book with their infant just as they would at home.
- **Parent-Child Interaction:** The examiner will let the parent and child freely interact for a 10-minute episode of videotaped, unstructured toy play. The dyad will sit on a floor mat with a small set of toys. The parent will be instructed to engage in play with the child as they typically would at home, with or without the toys.

Once the assessment is complete, the examiner will review with the parents how to re-pack the return shipping box for the materials. All assessment materials will be returned either via pre-paid box that can be scheduled for pickup at the family's convenience, or dropped off at a designated location, whichever the family prefers. The kits are returned to the team after each visit.

**TELE-ASD-PEDS:** A Telemedicine based ASD Evaluation Tool for Toddlers and Young Children. The TELE-ASD-PEDS was developed by researchers at Vanderbilt University to assess remotely autism symptomology. The TELE-ASD-PEDS will be administered during remote visits at 24- and 36-months, or, if the parent reported M-CHAT score is elevated and indicative of potential ASD symptomology, at 18 or 30 months. If the infant has received a diagnosis of autism prior to any of these timepoints, the protocol will not be completed.

*Bayley Scales of Infant and Toddler Development-III* (Bayley, 2006). The Bayley-III is a standardized measurement of early developmental skills across the areas of cognition, language, motor, and social-emotional abilities for infants 1-42 months.

*Peabody Developmental Motor Skills, 2nd edition (PDMS-2)* (Folio & Fewell, 2000) This early childhood motor development program contains six subtests that assess the motor skills of children from birth through 5 years.

*Autism Observation Scale for Infants (AOSI)* (Bryson et al., 2007). The AOSI 18-item direct observational measure designed to detect and monitor putative signs of autism in infants aged 6–18 months.

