### A.4.A. Biomedical methods and procedures

A.4.A.1. Is this an interventional study?

Yes

Distinguish what is being done specifically for this research from procedures that would be done anyway for clinical care:

Delays in diagnosis can reduce timely access to interventions that could have significant consequences for the developmental trajectories of these children. Through the Early Check Screening (IRB #18-0009), children who may typically not have been identified with these disorders until they display symptoms will be able to participate in early intervention services prior to the emergence of symptoms.

Next, assessment and coding procedures that would not be used in standard clinical practice will be used; measuring three broad outcome areas: social validity of PIXI, child development, and parent responsivity and efficacy.

Lastly, weekly family support sessions will be provided immediately following the diagnosis. All of the identified intervention models with any empirical basis have begun the direct intervention with infants after the age of 6 months—most start as late as 9 or 12 months. The Infant Start intervention model has been used with infants as young as 7 months; therefore, to maintain the integrity of that intervention, phase 2 of the intervention will start no earlier than when the infant is 6 months of age. However, per the Early Check protocol (IRB #18-0009), all of the infants will have been screened before 2 months of age, providing a gap of up to 4 months where infants and families will not be receiving formal intervention. It is proposed an initial phase of intervention that will involve regular but less formal contact with the family in the months between diagnosis and the start of the phase 2 intervention.

A.4.A.2. If the study involves the use of placebo control, provide justification

N/A

A.4.A.3. Will this study involve drugs, biologics or other substances (such as a botanical or dietary supplement)?  
For guidance on dietary supplements, see Section VI, C [FDA guidance document UCM229175.pdf](#)

No

A.4.A.4. Is there an Investigational New Drug application (IND) for this study?

No

Please check below:

- ☒ This study does not involve drugs, biologics or other substances.
- ☒ I am using a U.S. commercially available agent, consistent with labeling.

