## A.8. Data analysis

A.8.1. Summarize the statistical analysis strategy for each specific aim.

For this case series, analyses will be primarily descriptive. Researchers will first examine feasibility and acceptability and descriptive data on pre-post measures at the case level. Next, change scores on each measure over the intervention period will be reviewed to help identify primary outcome measures and effect sizes for a larger trial. Finally, the team will compare developmental and behavior profiles of this sample at age 3 to those of young children with the disorder who were not identified through Early Check (IRB #18-0009).

A.8.2. If this is a pilot study, please describe the future study and say how its study design, aims, sample size, and methods differ from the pilot study you are proposing.

Upon completion of the case series, the team will use data collected on family needs, acceptability and feasibility of the intervention, child skills, parent responsivity, and social validity to refine (1) PIXI and develop a formalized treatment manual for all components, (2) our hypotheses about treatment effects, and (3) our measurement plan. A meeting will be held with consultants and Early Check expert advisors during year 2 of this project to review results and plan next steps. It is anticipated revisions to include manualizing the content and strategies incorporated into parent calls, timing and telehealth revisions, possible adaptations to phase 2 necessary for unique needs of those with rare neurogenetic disorders, and development of fidelity measures for all components.

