NOTE: Investigators utilizing ANY federal funding to conduct this research should review the [COC website](#) to determine if their funding agency issues COCs automatically (as the NIH does) or if they might need to apply for the COC via the online COC system. Unfunded and non-federally funded investigators may also apply for a COC via [the online COC system](#).

No

A.10.5. If this study is limited to data collection by survey or interview, discuss the potential for deductive disclosure (i.e., directly identifying subjects from a combination of indirect IDs).

The primary potential for deductive disclosure will be through videotaping of research participants. Videotapes

of intervention sessions will be viewed and coded for parent responsivity. Videotapes will have full face images of children and family and it is likely first names will be used throughout the interaction with interventionist, creating a potential for identification. We, therefore, will take careful measures to protect the security of videotapes. The IDs used for other assessments and materials offer little potential for deductive disclosure.

A.10.6. Will any of the groupings or subgroupings used in analysis be small enough to allow individuals to be identified?

Yes

Describe these groupings and sample sizes projected.

There is a possibility that participating individuals could be identified based on knowledge of infants who have a confirmed positive diagnosis of a rare disorder. Even with the most liberal of estimates of uptake for the Early Check program (IRB #18-0009), we would still only anticipate identifying around 10-20 infants per year.

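### Parenting efficacy is a named outcome with no measure in the schedule, and parent responsivity has no stated pre-intervention score

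*Protocol*

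**What the plan says.** Aim 2 in A.1.2 is to test preliminary effects on infants and parents. On the parent side it states: "Parental outcomes include parenting efficacy". A.4.A.1 describes the assessment and coding procedures as "measuring three broad outcome areas: social validity of PIXI, child development, and parent responsivity and efficacy". A.8.2 later lists child outcomes, parent responsivity and social validity as the three areas measured in the case series, without efficacy.

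The design in A.4.2 is an "open trial of PIXI with a pre-post design". Under A.8.1, "change scores on each measure over the intervention period will be reviewed" to help choose outcome measures and effect sizes for a larger trial.

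Two places give the source of responsivity coding. In the Phase 2 description (A.4.2, item 7): "Video recordings will later be coded for parent responsivity and fidelity"; the account of the earlier iBASIS-VIPP version in the same item likewise points to its session recordings. In A.10.5, videotapes "of intervention sessions will be viewed and coded for parent responsivity".

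Separately, the remote PANDABox battery includes a task in which parent and child "freely interact for a 10-minute episode of videotaped, unstructured toy play". The protocol assigns no responsivity code to it.

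**The concern.** A pre-post design can report change only in what is measured both before and after. Here the parental outcome named in the aims is not tied to any measure. The second parent outcome, responsivity, is tied to video that begins when part of the intervention has already been delivered. A.8.1 uses change scores to select outcomes and effect sizes for the next trial, and A.8.2 carries responsivity into that trial. An outcome with no measure, or with no baseline, cannot inform those choices. A questionnaire value missed at Time 1 cannot be recovered later, so the gap grows while enrolment stays open.

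**Working it through.** The plan derives no figure on this point. The check sets the named outcomes against the schedule, the measure descriptions and the attachment list.

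**Step 1: parenting efficacy.** These are the nine rows under Parent Report: Self, with the number of marks in the Table of Measures and the construct given in the descriptions:

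- Parent Engagement Intervention, 2 marks: a motivational module to support attendance and home practice, not an outcome scale
- Demographics, 7 marks
- Edinburgh, 3 marks: depressive symptoms
- PHQ-9, 4 marks: depression
- BRIEF2A, 1 mark: executive functioning
- STAI, 6 marks: anxiety
- PSI-4 SF, 6 marks: stress in the parent-child relationship
- MOS-SSS, 6 marks: social support
- Social Validity and Parent Interview, 2 marks: satisfaction and perceived effects, placed at Times 2 and 3

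Rows described as measuring parenting efficacy: 0 of 9. The other rows cover the child. No attachment title names an efficacy scale. A change score is the later value minus the Time 1 value, and for efficacy neither term exists.

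**Step 2: responsivity.** The sequence in A.4.2 is Time 1, Phase 1, Time 2, Phase 2, Time 3. Phase 1 sessions already use parent coaching techniques. Phase 1 calls are audio recorded and coded for what parents report about development, not for responsivity. The first video with a stated responsivity code is therefore in Phase 2.

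- Change over the intervention period: Time 3 minus Time 1. No responsivity score is stated for either point.
- Change available from the stated source: last Phase 2 session minus first Phase 2 session. This leaves out Phase 1.

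**Step 3: another source.** PANDABox is described as given at every time point when the assessment is remote, and it holds the uncoached 10-minute interaction. That would supply Times 1, 2 and 3 for families assessed remotely, with three limits:

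- The modification summary speaks of selected PANDABox components alongside the DAYC-2, so the episode must be among those kept.
- Results shared from an outside provider or study may not include it.
- The protocol does not say how many families have a remote Time 1.

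**Step 4: how much can still be recovered.** The modification form gives 30 subjects enrolled, and A.2 plans 120. So 30/120 = 25% are enrolled and 120 − 30 = 90 remain. Assuming that both counts include one parent and one infant per family, this is 15 families enrolled and 45 still to come.

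**The case against.** The strongest reply is that the wording of A.1.2 is not exhaustive and that parent data are plentiful. PSI-4 SF, STAI and MOS-SSS carry six marks each, the depression scales are repeated, and A.8.1 covers each measure. This stands. A reader might infer that the parent side of aim 2 cannot be answered at all; the documents do not support that. The gap concerns the outcome that the aims name.

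Second, a reader might infer that all session video shows coached behaviour. That also goes too far: the first Phase 2 session is for goal setting, with an informal play assessment. A change within Phase 2 can therefore be described. Because Phase 1 coaching precedes it, it is still not a pre-intervention comparison.

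Third, the choice of clips and coding scheme may sit in a coding manual or analysis plan not shown, and neither coding statement excludes other sources. This is fair for responsivity, and it is why the finding is that no pre-intervention score is specified, not that none is possible. It does not help efficacy, because no analysis plan can supply data that the schedule does not collect. Early Check family assessments count as baseline and are not fully shown. Even if they held an efficacy scale, this schedule has no later one to compare with it.

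Fourth, it is tempting to treat the Adamson Engagement States coding as a source of in-person video. Its description covers the segmenting of the child's activity and mentions no parent-child recording, so that cannot be assumed.

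**Conclusion.** The concern holds in this limited form. Parenting efficacy is named in A.1.2 and A.4.A.1 and measured by 0 of the 9 parent self-report rows, so the plan as written yields no pre-post data on it. Responsivity has a stated coding source only in session video that begins after Phase 1, so the change planned in A.8.1 has no specified baseline. A.1.2, A.4.A.1 and A.8.2 also name three different sets of parent outcomes and need to be reconciled.

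This rests on the measures as the protocol describes them. If the sponsor intends an existing scale to stand for efficacy, the protocol must say so. Child outcomes, feasibility, acceptability and the other parent measures are unaffected. The study is a descriptive pilot meant partly to refine its measurement plan, so this should be fixed but is not disqualifying.

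**What to change.** 1. In A.1.2 and A.4.A.1, take one of two routes, and align A.8.2 with the choice.
   - Replace parenting efficacy with the parent outcomes actually collected, for example parenting stress on PSI-4 SF and observed responsivity. This costs wording only.
   - Add one short parenting self-efficacy questionnaire at Times 1, 2 and 3. This costs a few minutes of parent time at each point, and families already past baseline will have no Time 1 value.
2. For families assessed remotely, code responsivity from the uncoached 10-minute PANDABox interaction at Times 1, 2 and 3. State that this episode is always among the components kept. Mask coders to time point where feasible. The cost is coding time on a recording that the battery already makes.
3. For families assessed in person, use an equivalent assessment recording only if the sponsor confirms that one exists. Otherwise state that responsivity change is available for remote families only.
4. Report any change across Phase 2 session videos as within-phase change, not as pre-post change.
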